**Methods and analysis::**

Randomized clinical trial in 287 PCCs, formed by 2 groups (intervention and control). Population: patients controlled in PCCs, diagnosed with NVAF 1 year before the implementation of the decision support tool and with VKA treatment over a minimum of 1 year. A simple randomization method will be performed at a sector level. The decision support tool will be available for 1 year. The time in therapeutic range (TTR) will be available in the digital clinical history only to professionals of the intervention group. The information system for primary care research development database will be used for the data extraction. Statistical analysis will be done at 3 time points: before the implementation of the tool, at 1 year, and at 2 years after the beginning of the intervention. Multilevel (patient and professional levels) logistic regression models will be used to estimate the effect of the intervention.

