### Study design and setting

2.1

A cluster, randomized, clinical trial (type: parallel group) will be performed with patients attended in the ICS primary care setting. It is estimated that 5.8 million people are attended in ICS which comprises 287 PCCs around Catalunya (source: Sistemes d’Informació dels Serveis d’Atenció Primària (SISAP) of the ICS, unpublished data).

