### Randomization

2.5

The randomization will be made by sectors of the ICS. A sector is a group of PCCs that share 1 computer server. The ICS has 15 sectors. The sectors will be randomized using a simple randomization method. From the generation of random numbers (between 0 and 1) 2 groups will be created so that the numbers with which the first decimal is <5 will be rounded down to 0 and the remaining will be rounded up to 1. The sectors associated with 0 will constitute the control group and those associated with 1 will make up the intervention group. The study flowchart is presented in Figure 1.

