### Statistical analysis

2.10

The statistical analysis will be performed at 3 time points: before the implementation of the CDS-NVAF (baseline), at 1 year after the beginning of the intervention (1-year follow-up), and at 2 years after the beginning of the intervention (2-year follow-up).

A descriptive analysis of all the variables studied will be carried out using frequency and percentage for categorical variables and mean, standard deviation, minimum, median, and maximum for continuous variables. The Students’ *t* test (or the Mann–Whitney U test in cases not fulfilling the criteria of normality) will be used to determine possible differences in the means of the quantitative variables between the 2 study groups. The Chi-square test (or Fisher exact test) will be used for the qualitative variables. The rates of incidence for each variable will be expressed as patient/years with the corresponding confidence intervals of 95%.

Analysis at a professional level: a logistic regression model will be used to search for possible associations among the primary outcome variables and the secondary variables. First, each variable will be evaluated separately by univariate models and all the variables that are statistically significant or have a *P* ≤ .10 will be included in the multivariate model.

Analysis at a patient level: at this level hierarchal or multilevel methods will be used to take into account the structure of the data and to be able to introduce the variables of the patient in the estimation of the effect of the intervention. The levels will be professional (level 2) and patient (level 1). Multilevel logistic regression models will be made to estimate the effect of the intervention. The strategy of the analysis will be to estimate the effect of the intervention considering professionals as the random part. Afterwards, we will estimate the effect by introducing the variables of quality of care of the professional level (SQPP and SHCQ) and finally, we will study whether the introduction of patient variables modifies the effect of the intervention.

The level of significance will be set at 5% and the statistical package IBM SPSS Statistics v.23.0 for Windows will be used to perform the statistical analyses.

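### Fifteen sectors are randomised, but the effect model stops at the professional level, so its standard errors leave out between-sector variation and the 5% test rejects too often

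*Protocol article*

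**What the plan says.** Protocol article, section 2.5 (Randomization): "The randomization will be made by sectors of the ICS". A sector lies above the primary care centre: "A sector is a group of PCCs that share 1 computer server". "The ICS has 15 sectors", and the split between arms is left to chance: "The sectors will be randomized using a simple randomization method". Section 2.1 puts the number of centres under those sectors at 287.

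Section 2.10 (Statistical analysis) fixes the effect model as multilevel logistic regression: "The levels will be professional (level 2) and patient (level 1". The strategy is to "estimate the effect of the intervention considering professionals as the random part". Later steps add the two professional quality scores and then patient variables; none adds centre or sector. The abstract has the same structure: "Multilevel (patient and professional levels) logistic regression models will be used to estimate the effect of the intervention".

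Section 2.4 (Sample size) mentions a correction for clustering, but gives neither the level nor the ICC.

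**The concern.** The tool is switched on or off for a whole sector, so the arms can differ by chance in everything that varies between sectors. The outcomes section (2.8.2) lists such features itself: urban or rural setting, deprivation index, and quality of care and of prescribing. A random intercept for professionals averages this variation over all professionals in an arm. In truth it averages over only the sectors in that arm, about 7 or 8 if the split is near even.

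The result is standard errors that are too small, confidence intervals that are too narrow and P values that are too low for the primary outcomes. A chance difference between groups of sectors can then be reported as benefit or harm of the tool. The Discussion foresees extending the tool across the ICS if results are good, so a false positive would have practical consequences.

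**Working it through.** **Inputs from the protocol article.** 15 sectors (2.5); 73,632 anticoagulated patients, of whom 63,001 are on VKA, and 10% loss (2.4); thromboembolic rate 0.66% (2.4); significance level 5% (2.10), taken as two-sided.

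**Assumptions, because the document gives no figure.** 20 patients per professional; professional ICC ρp of 0.01 or 0.05; sector ICC ρs from 0.0001 to 0.005.

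**Patients per sector.** 73,632 / 15 = 4,909; after loss, 73,632 × 0.9 / 15 = 4,418. VKA patients only: 63,001 × 0.9 / 15 = 3,780.

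**Variance ratio.** Patients of one professional share both components, so their correlation is ρp + ρs. Patients of different professionals in one sector share ρs.

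- Design effect seen by the planned model: A = 1 + 19 × (ρp + ρs)
- Actual design effect: B = A + (4,418 − 20) × ρs
- True type I error = 2 × [1 − Φ(1.96 / √(B/A))]

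Example with ρp = 0.01 and ρs = 0.001: A = 1 + 19 × 0.011 = 1.209; B = 1.209 + 4,398 × 0.001 = 5.607; B/A = 4.64; 1.96 / √4.64 = 0.91; type I error = 36%.

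| Sector ICC | B/A (ρp = 0.01) | Type I (ρp = 0.01) | Type I (ρp = 0.05) |
|---|---|---|---|
| 0.0001 | 1.37 | 9% | 8% |
| 0.0005 | 2.83 | 24% | 18% |
| 0.001 | 4.64 | 36% | 28% |
| 0.005 | 18.1 | 65% | 57% |

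**Sensitivity to sector size** (ρp = 0.01, ρs = 0.001): 4,418 patients gives 36%, 3,780 gives 33%, and an illustrative 2,000 gives 23%.

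**Simulation under no effect.** 2,000 trials per setting; 15 sectors by simple randomisation with at least 2 per arm; 221 professionals per sector with 20 patients each; professional SD 0.3 on the logit scale. A test with professionals as independent units stands in for the planned model. It is compared with a t-test on the 15 sector means.

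| Between-sector SD (logit) | Professional as unit, 0.66% rate | Professional as unit, 50% rate (assumed) |
|---|---|---|
| 0 | 5.2% | 5.6% |
| 0.05 | 6.5% | 25% |
| 0.1 | 8.9% | 50% |
| 0.2 | 17.8% | 72% |
| 0.3 | 31.6% | 80% |

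With no sector variation the nominal 5% is reproduced, so the excess in the other rows comes from the missing level. The sector-level t-test stayed between 4.2% and 5.9% in all ten settings.

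**Reference distribution.** 15 sectors in two arms leave 15 − 2 = 13 degrees of freedom, with a critical value of 2.16 instead of 1.96.

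**The case against.** Five points can be made for the plan.

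- **The size depends on an ICC that nobody has stated.** This stands. The upper end of the range also suits rare events poorly. At a 0.66% rate, a sector ICC of 0.005 means a between-sector SD of √(0.005 × 0.0066 × 0.9934) = 0.57 percentage points, or 87% of the mean rate. For thromboembolic events the simulated 6.5% to 32% is the better guide. For a common outcome the same ICC is unremarkable: at 50% it is an SD of 3.5 points.
- **Sectors may hold fewer analysed patients than 4,418.** This also stands. The abstract limits the population to VKA patients, and section 2.2 requires at least 6 INR controls and excludes hospital INR follow-up. The sensitivity figures show that the inflation shrinks but remains.
- **A 7 to 8 split is not fixed.** True: under simple randomisation it has probability 2 × 6,435 / 32,768 = 0.39. A split of 5 to 10 or worse has probability 0.30. An uneven split lowers precision, so this does not help the plan.
- **The t, Mann-Whitney, chi-square and Fisher tests are descriptive, and the professional-level regression is exploratory.** This is a fair reading. The finding rests on the multilevel model, which is the one assigned to the intervention effect.
- **The sample size was corrected for clustering, and an analysis plan could add the missing level.** Neither point rescues the text. A larger sample does not correct a test that omits the randomised unit. The levels are not left open either: the abstract and section 2.10 both name them.

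**Conclusion.** The plan is wrong as written and must be corrected before analysis. That the randomised unit is missing from the effect model follows directly from the text and needs no assumption. Type I error exceeds 5% whenever between-sector variance is above zero.

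How far it exceeds 5% depends on the outcome and on the unstated sector ICC. For the thromboembolic rate it runs from modest to serious over the range examined. For adequacy of treatment, if its frequency is anywhere near the assumed 50%, even a between-sector SD of 0.05 on the logit scale takes the error to about 25%.

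**What to change.** In section 2.10, make sector the top level of the model: patient, professional, centre if the data support it, and sector. Give sector a random intercept and test the intervention effect with small-sample degrees of freedom (about 13). Two alternatives are equally sound and simpler: a two-stage analysis with a t-test on the 15 sector summaries, or a permutation test over the possible sector allocations given the split obtained.

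Use the same sector-based variance for any other between-arm test that is reported and for the 95% intervals of the incidence rates. Bring the abstract into line. State in section 2.4 the level and the ICC behind the cluster correction, and check the stated power on that basis.

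The change costs wording and some programming. Sector follows from the centre, which is already recorded. The real price is precision: at ρp = 0.01 and ρs = 0.001, intervals widen by about √4.64 × 2.16 / 1.96 = 2.4 times. That lowers the power that can be claimed, but the narrower intervals were never justified by the design.

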Despite the increasingly more frequent use of computerized medical reminders, few studies have assessed their impact on health outcomes.^[17–21]^ A systematic review showed that notifications influence specific aspects of the prescription process and may be an effective method to reduce the prescription of contraindicated medications, although their impact on health outcomes was not demonstrated.^[22]^ Within the primary care setting it was found that computerized clinical notifications significantly improved the adequacy of treatment in patients with poorly controlled asthma and consequently reduced the rate of reexacerbations during follow-up. Moreover, medical professionals considered these reminders to be particularly useful for the identification of patients with bad control.^[23]^

The present project aims to evaluate the impact of the implementation of a clinical decision support tool associated with the electronic clinical history which informs healthcare professionals of the TTR in patients with NVAF attended in primary care centers (PCCs) of the ICS. This project will evaluate the impact of this tool on the adequacy of anticoagulant treatment, the incidence of thromboembolic and hemorrhagic complications, and mortality at 2 years after the beginning of the intervention. The evaluation of the impact of the intervention will be performed based on the characteristics of the patients and the healthcare professionals.

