#### Secondary outcomes

2.8.2

(1)Sociodemographic characteristics of the patients: age, sex, primary care area assigned, physician assigned;(2)PCC characteristics: teaching center, urban/rural, socioeconomic deprivation index (MEDEA), standard of healthcare quality (SHCQ) and the standard of quality of pharmaceutical prescription (SQPP);(3)Characteristics of the professional: age, sex, PCC, type of work contract, SHCQ, SQPP;(4)Type of anticoagulant treatment: DOAC (dabigatran, apixaban or rivaroxaban), VKA (acenocoumarol or warfarin), heparin (with starting and completion date);(5)Type of treatment with risk of bleeding: antiaggregants, nonsteroidal anti-inflammatories, and selective serotonin reuptake inhibitors (with starting and completion date);(6)Thromboembolic risk CHA2DS2-VASC (congestive heart failure, hypertension, age 75 years or older, diabetes mellitus, previous stroke or TIA, vascular disease, age 65–74 years, female) score (with date of determination). The score indicates the risk of a patient with NVAF of suffering a stroke in 1 year. The score goes from 0 (absence of risk) to 10 (greater risk);(7)Bleeding risk HAS-BLED (hypertension, abnormal liver/renal function, stroke, bleeding history or predisposition, labile INR, elderly (>65 years), and drugs/alcohol) score (with date of determination). The score allows the calculation of the risk of bleeding in patients with NVAF receiving oral anticoagulant treatment based on the risk factors associated with the probability of bleeding. Score: 0 = low risk; 1 = intermediate risk; 2 = intermediate risk; ≥3 = high risk;(8)Associated comorbidity (with date of diagnosis): diabetes mellitus, arterial hypertension, heart failure, chronic kidney failure, nephropathy, abnormal liver function, alcoholism, peripheral vascular disease, stroke, peripheral embolism, or TIA;(9)Other determinations (with date of determination): creatinine, systolic blood pressure, and ejection fraction.

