With regard to the limitations of the study, the SIDIAP database includes secondary data, and thus, there may be a certain level of underregistration of variables of interest, although this should not differ between the 2 study groups. The quality of the registry is guaranteed in that most of the study variables make up part of different indicators of quality (SHCQ and SQPP) which are incentivated in the payment systems for objectives of the ICS. There is no problem in the registry of the treatment variables as the billing system of the pharmacy offices collects these data. Another limitation is that the study is unblinded for physicians and there may be contamination between groups which may limit the conclusions of the study. Nonetheless, we aim to evaluate the effectiveness of the intervention in the real-life setting related to the usual clinical practice in which this type of situation is frequent. The investigative team believes that randomization by sectors and not by physicians will reduce the probability of contamination between groups. Another limitation of the study is that the tool provides information about the adequacy of the VKA but not the adequacy of the DOACs, which should be taken into account in result interpretation.

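### Movement of the arm coefficient between successive logistic models does not show whether the tool works differently by patient or professional, and covariates in those models should be dated before activation

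*Protocol article*

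**What the plan says.** The last sentence of the Introduction that describes the project reads: "The evaluation of the impact of the intervention will be performed based on the characteristics of the patients and the healthcare professionals".

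Section 2.10 (Statistical analysis) then sets out the patient-level analysis. Its stated purpose includes "to be able to introduce the variables of the patient in the estimation of the effect of the intervention". Three steps follow:

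1. "The strategy of the analysis will be to estimate the effect of the intervention considering professionals as the random part".
2. "we will estimate the effect by introducing the variables of quality of care of the professional level (SQPP and SHCQ", the two quality standards for prescribing and for care.
3. Finally, "we will study whether the introduction of patient variables modifies the effect of the intervention".

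The text states no arm-by-characteristic term, stratified estimate or subgroup analysis. The separate professional-level analysis in 2.10 looks for associations between outcomes and the secondary variables after univariate screening. That is not a comparison of the arm effect across characteristics either.

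Two other places bear on which covariates are used. The limitations paragraph of the Discussion says that "most of the study variables make up part of different indicators of quality (SHCQ and SQPP" are the scores in question. Section 2.8.2 lists, among the secondary variables, "Type of anticoagulant treatment: DOAC (dabigatran, apixaban or rivaroxaban), VKA (acenocoumarol or warfarin), heparin (with starting and completion date". It also lists HAS-BLED, which contains labile INR, and comorbidities that include stroke, peripheral embolism and TIA.

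**The concern.** Whether an effect differs by characteristic is a question about the arm effect within levels of that characteristic. Section 2.10 instead looks at whether one overall arm coefficient changes when variables are added. In a logistic model the two are different things. The coefficient can change with no modification at all, because the OR is not collapsible or because the covariate was imbalanced between arms. It can also stay put when one group benefits and another does not. A reader of the results could then be told that patient variables modify the effect when they do not, or that they do not when they do.

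The second matter is which values of the covariates are used. If scores built partly from study variables are measured after the tool is switched on, they can carry part of the intervention's effect. Conditioning on them would then shrink the second- and third-step estimates. Section 2.10 does not say which of the three estimates is the main one.

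**Working it through.** The protocol gives no figure on this point, and no adequacy rate, covariate effect or expected OR for adequacy, so there is nothing to reproduce. Every rate and OR below is an assumption chosen to show the mechanism, apart from 0.66% and the 10% relative reduction, which are in section 2.4. Arms are equal in size and covariates balanced. The professional random effect is left out.

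**A. The coefficient moves although the effect is constant.** Assume 60% adequacy in controls, a conditional OR of 1.50 for everyone, and a normal prognostic covariate with standard deviation s on the log-odds scale.

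- Choose a so that the mean of expit(a + s·z) over a standard normal z is 0.60.
- The intervention proportion p1 is the mean of expit(a + ln 1.5 + s·z).
- The unadjusted OR is [p1/(1 − p1)] / (0.60/0.40).

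With s = 1.0: p1 = 0.6778, so the OR is (0.6778/0.3222)/1.5 = 1.40. With s = 1.5: p1 = 0.6672, so the OR is (0.6672/0.3328)/1.5 = 1.34. Adding the covariate returns 1.50 in both cases.

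**B. The coefficient stays still although the effect differs.** Take two equal halves with control adequacy of 50% and 70% (mean 60%) and true ORs of 2.0 and 1.0.

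- Intervention adequacy: 2/3 in the first half and 0.70 in the second, mean 0.6833.
- OR without the modifier: (0.6833/0.3167)/1.5 = 1.44.
- OR with the modifier added as a main effect (logistic fit to the expected proportions): 1.45.
- With an arm-by-half term, the fit returns 2.0 and 1.0 exactly.

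**C. Same covariate, with and without modification.** A balanced binary covariate has the covariate OR shown, fitted to expected proportions:

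| Covariate OR | True arm ORs in the two strata | Arm OR before | Arm OR after |
|---|---|---|---|
| 2.7 | 1.5 and 1.5 | 1.46 | 1.50 |
| 7.4 | 1.5 and 1.5 | 1.38 | 1.50 |
| 7.4 | 2.0 and 1.0 | 1.37 | 1.45 |
| 7.4 | 2.0 and 0.5 | 1.00 | 1.00 |

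In this table the largest movement occurs where there is no modification, and the smallest where the strata differ most.

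**D. Rare events.** Repeat A with a control rate of 0.66%. With s = 1.0 a conditional OR of 1.50 appears as 1.49. A conditional OR of 0.90, roughly the 10% relative reduction in section 2.4, appears as 0.90 with s = 1.0 or s = 1.5. The shift in A therefore matters for adequacy and is negligible for thromboembolic events. That a single coefficient does not show subgroup differences holds for any outcome.

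**E. Post-activation covariates: the direction only.** In the extreme case, the whole effect passes through one variable measured after activation. Assume 10% v 30% switching, 50% adequacy without a switch, and a switch-outcome OR of 20 (adequacy 20/21 with a switch).

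- Control: 0.9×0.5 + 0.1×20/21 = 0.5452.
- Intervention: 0.7×0.5 + 0.3×20/21 = 0.6357.
- OR: (0.6357/0.3643)/(0.5452/0.4548) = 1.46.

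Conditional on the switch variable, the OR is 1.00 by construction. This shows the mechanism at its limit. It does not estimate what adjustment for SQPP or SHCQ would do, since the documents do not say how strongly those scores track adequacy.

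**The case against.** The strongest reply is that the sentence describes adjustment. What is said to modify the effect is the introduction of variables, and the stated purpose is to bring patient variables into the estimation. Adjustment has a sound motive here, because only 15 sectors are randomised by a simple method and chance imbalance is likely. This reading is open, and no subgroup conclusion is formally announced. It does not close the point. Under that reading the Introduction's statement has no suitable method in the text, and the word used still invites a claim of effect modification. A reader might infer that the plan is incapable of answering its own question. That goes too far, because the Introduction's sentence is itself loosely worded.

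It can also be said that model terms belong in an analysis plan that is not shown. That holds for finer detail, but section 2.10 itself chose the steps and the criterion.

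On the covariates, a reader might infer that the plan will adjust for follow-up quality scores, or for the anticoagulant the tool is meant to change. The documents do not support that. Table 1, the collection schedule, is not shown. Treatments, scores and diagnoses are recorded with dates, so earlier values can be selected. The patient-level model names SQPP, SHCQ and unspecified patient variables, not type of anticoagulant. The Discussion's remark concerns recording quality and does not say that adequacy or TTR forms part of either score. All of this stands, so attenuation remains only a possibility.

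**Conclusion.** The point holds in two parts of unequal strength.

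The first rests on what section 2.10 states. Comparing the arm coefficient before and after adding covariates cannot show whether the intervention works differently by patient or professional. The OR pairs above (1.40 to 1.50 with a constant effect, 1.44 to 1.45 with ORs of 2.0 and 1.0) illustrate this under assumed inputs and predict nothing about this trial. The paragraph should say which aim it serves.

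The second is a conditional risk. If SQPP, SHCQ or patient variables entered at the second or third step carry values dated after activation, those estimates could be drawn toward no effect. No percentage loss can be given from the documents. The first-step estimate contains no covariates and is not exposed. This is worth correcting before analysis, but it is not a defect in the basic effect estimate.

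**What to change.** In section 2.10:

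1. Replace the sentence on whether introducing patient variables modifies the effect with arm-by-characteristic interaction terms for a short, pre-named list of patient and professional characteristics. Report the arm effect with its 95% confidence interval at each level, and label these analyses secondary.
2. State that SQPP, SHCQ and any patient scores, comorbidities or treatment variables enter the effect models only with values dated before the tool was activated.
3. Name the model without post-activation covariates as the main estimate of the intervention effect, and describe the covariate steps as adjusted analyses.

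The cost is a few sentences and model terms, and no new data, since the listed variables already carry dates. The downside is that interaction estimates will have wide intervals and should not be over-read.

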### Sample size

2.4

In a first approach the information system for primary care research development (SIDIAP) established that during 2015 PCCs of the ICS had registered 171,472 cases of NVAF, 73,632 of whom were receiving anticoagulant treatment (63,001 VKAs and 10,631 DOACs). Assuming a weight of 90%, an alpha error of 5%, a control versus intervention ratio of 1, corrected for the design by clusters and assuming a loss of 10%, our study will be able to detect a difference of 1% for a rate of thromboembolic events of 0.66%. Despite this power, a clinically relevant relative reduction of 10% will be established.

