#### Primary outcomes

2.8.1

(1)Incidence rate of thromboembolic events (acute myocardial infarction or angina, ischemic stroke, peripheral embolism, or transient ischemic attack [TIA]).(2)Incidence rates: Hemorrhagic events (intracranial hemorrhage, gastrointestinal hemorrhage); All-cause mortality.(3)Adequacy of anticoagulant treatment: This variable encompasses the adequacy of the anticoagulant treatment, taking into account if an adequate change has occurred or not. The adequacy of the AT in patients with NVAF will be based on the fulfillment of the criteria of the ministry of health, social services and equality of Spain, 2016^[11]^ (Table 2).

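### Four unranked primary outcomes are analysed at 1 and 2 years under one undivided 5% level, so the chance of a false positive primary result can be well above 5%

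*Protocol article*

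**What the plan says.** Section 2.8.1 (Primary outcomes) has three numbered items that contain four endpoints:

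- Item 1: "Incidence rate of thromboembolic events".
- Item 2, which holds two endpoints: "Hemorrhagic events (intracranial hemorrhage, gastrointestinal hemorrhage); All-cause mortality".
- Item 3: "Adequacy of anticoagulant treatment: This variable encompasses the adequacy of the anticoagulant treatment", scored 0 or 1.

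None is ranked above the others. Section 2.10 (Statistical analysis) places the analyses at baseline, "at 1 year after the beginning of the intervention (1-year follow-up), and at 2 years after the beginning of the intervention (2-year follow-up"). For the treatment comparison it says "Multilevel logistic regression models will be made to estimate the effect of the intervention", without singling out an outcome or a date. It then states "The level of significance will be set at 5" per cent, once, for everything.

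Section 2.4 (Sample size) uses "an alpha error of 5" per cent and an event rate for thromboembolic events only. The Introduction sets the evaluation of adequacy, complications and "mortality at 2 years after the beginning of the intervention". It does not say that the 1-year analysis is descriptive.

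**The concern.** A 5% level limits the false positive chance to 5% for one test. Here four outcomes share the primary label and each is analysed at two dates after the start of the intervention. The article therefore provides up to eight primary comparisons, each at the full 5%.

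The text gives no consistent implied order either. The Abstract and Introduction name adequacy first in the aim, while sections 2.4 and 2.8.1 lead with thromboembolic events.

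This matters because the outcomes support different claims. Adequacy is a prescribing measure that the alert acts on directly; the other three are health outcomes. The Introduction itself notes that an effect of such notifications on health outcomes had not been shown. The Discussion foresees extending the tool across the ICS if the results are good, without defining a good result. As written, the outcome and date that support such a decision could be chosen after the results are seen.

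**Working it through.** **Inputs from the article.** Level 5% (sections 2.4 and 2.10); four primary outcomes (2.8.1); two analyses after baseline (2.10); 90% in section 2.4, printed as a weight and read here as power.

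**Assumptions not in the article.** Tests are two-sided. Any one significant primary result counts as success. Data are cumulative with half the information at 1 year, so the 1- and 2-year statistics correlate at √0.5 = 0.71. Each test is valid for the clustered design. Correlations between outcomes are unknown and are varied below.

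**Step 1: the stated level.** One outcome at one date: 1 − 0.95 = 5%. The stated figure is correct for a single test.

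**Step 2: four outcomes, one date.** If independent, 1 − 0.95⁴ = 1 − 0.8145 = 18.5%. The upper bound under any correlation is 4 × 5% = 20%.

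**Step 3: both dates.** For one outcome, the bivariate normal probability that |Z| exceeds 1.96 at either date, with correlation 0.71, is 8.31%. For four independent outcomes, 1 − (1 − 0.0831)⁴ = 29.3%. If the correlation between dates is 0.8 or 0.9 instead, the result is 27.8% or 25.3%. Eight fully independent tests would give 1 − 0.95⁸ = 33.7%.

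**Step 4: correlated outcomes.** The first row is from the formulas above; the others are from simulation with 1,000,000 replicates and a correlation of 0.71 between dates.

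| Correlation between outcomes | One date | Both dates |
|---|---|---|
| 0 | 18.5% | 29.3% |
| 0.3 | 17.4% | 27.6% |
| 0.5 | 15.6% | 24.8% |
| 0.7 | 13.1% | 20.8% |
| 0.9 | 9.4% | 15.2% |

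**Step 5: other ways of counting.** Treating item 2 as one outcome leaves three: 1 − 0.95³ = 14.3% at one date and 1 − (1 − 0.0831)³ = 22.9% over both. Counting only false positives in favour of the tool, four independent tests at one date give 1 − 0.975⁴ = 9.6%, against 2.5% for a single test.

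**Step 6: what control would cost.** Holm over four outcomes starts at 0.05/4 = 0.0125. Four independent tests at that level give 1 − 0.9875⁴ = 4.9%, and the bound of 5% holds under any correlation. A test with 90% power at two-sided 5% has an expected Z of 1.960 + 1.282 = 3.242. The critical value at 1.25% is 2.498, so power is Φ(3.242 − 2.498) = Φ(0.744) ≈ 77%. Restoring 90% needs ((2.498 + 1.282)/3.242)² ≈ 1.36 times the information.

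**The case against.** **An adjustment may be set out elsewhere.** Details of alpha allocation often sit in a statistical analysis plan, and none is shown here. A reader might infer that the trial has rejected any adjustment; the article does not say so. What stands is narrower. The four primary labels, the two analysis dates, the single 5% and the one-outcome sample size are choices the article makes, and it does not hand their reconciliation to another document.

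**The success rule is inferred.** A reader might take the plan to say that any of eight significant tests makes the trial positive. It states no such rule, and section 2.10 is worded in terms of estimation. This stands, and every percentage above depends on that reading. But the article also has no rule that requires all outcomes to succeed or ranks them, so nothing excludes it.

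**The date is partly settled.** The Introduction points to 2 years. If that is the only confirmatory date, the two-date figures fall away and 13–19% remains. Section 2.10, however, treats the two dates alike.

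**Independence is unlikely.** A fatal stroke or intracranial bleed also counts as a death, and section 2.12 (Safety) expects treatment changes to move both thromboembolic and hemorrhagic rates. This stands and is why ranges are given. The 0.71 is also an assumption, and adequacy, a status, need not accumulate as events do.

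**Hemorrhage components.** A reader might add separate tests for intracranial and gastrointestinal bleeding. The article lists these as components in parentheses, as it does for thromboembolic events, and plans no separate tests. They are not counted.

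**Conclusion.** The point holds as a conditional one. With four unranked primary outcomes and an undivided 5%, and if one significant result is enough, the chance of at least one false positive is about 13–19% at a single date and about 21–29% over both. The lower ends correspond to an outcome correlation of 0.7, the upper ends to independence. Even at a correlation of 0.9 the figures are 9.4% and 15.2%, so the excess over 5% does not depend on independence.

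None of these is the trial's established error rate. They rest on the inferred success rule, two-sided tests, the assumed 0.71 between dates, and tests that are valid for the clustering. The last is not secured by the text: section 2.5 randomises 15 sectors, while section 2.10 models only the professional and patient levels. That is a separate matter, but a multiplicity correction cannot repair p-values that are themselves invalid. The plan should be changed on this point; the change concerns decision rules, not the conduct of the trial.

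**What to change.** State in sections 2.8.1 and 2.10 that the 2-year analysis is confirmatory, in line with the Introduction, and that the 1-year analysis is supportive. Make thromboembolic events, the outcome used in section 2.4, the single primary outcome at 5%, and list hemorrhagic events, all-cause mortality and adequacy as secondary. This takes about two sentences and no new data, and it costs no power on thromboembolic events relative to testing them at 5%. The price is that the other three outcomes no longer carry a confirmatory claim.

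If all four are to remain primary, control them at an overall 5% with Holm at 2 years and state the cost. At the first step (1.25%), 90% power becomes about 77%, and keeping 90% would need about 36% more information, which section 2.4 does not set aside. Either choice should be recorded before outcome data are compared by group.
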